## Abstract

**Introduction:**

This study protocol outlines the evaluation of the pictorial support in person-centred care for children (PicPecc). PicPecc is a digital tool used by children aged 5–17 years to self-report symptoms of acute lymphoblastic leukaemia, who undergo high-dose methotrexate treatments. The design of the digital platform follows the principles of universal design using pictorial support to provide accessibility for all children regardless of communication or language challenges and thus facilitating international comparison.

**Methods and analysis:**

Both effect and process evaluations will be conducted. A crossover design will be used to measure the effect/outcome, and a mixed-methods design will be used to measure the process/implementation. The primary outcome in the effect evaluation will be self-reported distress. Secondary outcomes will be stress levels monitored via neuropeptides, neurosteroids and peripheral steroids indicated in plasma blood samples; frequency of in-app estimation of high levels of distress by the children; children's use of analgesic medicine and person centeredness evaluated via the questionnaire Visual CARE Measure. For the process evaluation, qualitative interviews will be carried out with children with cancer, their legal guardians and case-related healthcare professionals. These interviews will address experiences with PicPecc in terms of feasibility and frequency of use from the child’s perspective and value to the caseworker. Interview transcripts will be analysed using an interpretive description methodology.

**Ethics and dissemination:**

Ethical approval was obtained from the Swedish Ethical Review Authority (reference 2019-02392; 2020-02601; 2020-06226). Children, legal guardians, healthcare professionals, policymaking and research stakeholders will be involved in all stages of the research process according to Medical Research Council’s guidelines. Research findings will be presented at international cancer and paediatric conferences and published in scientific journals.

**Trial registration:**

ClinicalTrials.gov; NCT04433650.

Strengths and limitations of this studyA person-centred framework is used for the design of the intervention.A child-centred pictorially supported communication device is used for self-report from the age of 5 years.The study evaluates a complex intervention with a combination of self-reported symptoms and biomarkers.Biomarkers of stress are monitored via blood plasma.The process evaluation will give additional information for future usage based on the frequency and feasibility of use.

## Introduction

Children with cancer struggle with several physical and emotional symptoms. Their ability to communicate these symptoms is dependent on various factors such as age, maturity, diagnosis, cognitive status, psychological status, language ability and cultural background as well as situational aspects. Alleviating distress caused by cancer is beneficial for both children, their families and healthcare professionals^1^. Symptom identification and communicative support can enable symptom relief with the potential to reduce distress and alleviate suffering for the child and will also improve quality of the care.^1^

### Person-centred care for children

Person-centred care is found in ethics and based on the assumption that every person has resources that should be used in the care situation; being human is about having capabilities. This can be referred to Homo capax,^2^ that is, a person with capabilities and vulnerabilities, and who is considered responsible for his/her actions in relationships with others.^3^ There is no gold standard definition of person-centred care and the exploration of the concept has emphasised many different aspects and different definitions. In this project, the definition of person-centred paediatric care is based on three key concepts of partnership, narrative and documentation, generating a cocreated partnership and safeguarding the partnership through documenting the child’s narrative, preferences and participation.^4 5^

The project is found on the ethical principles put forward by the French philosopher Paul Ricœur, which aims for the good life, with and for others, with equitable and unbiased institutions.^6^ In this regards, a person-centred approach with a child perspective not only includes the idea of what is best for the child but also acknowledges the self-determination of the child. Decisions are, therefore, made that balance these concepts; that is, neither solely from an adult’s view of the child’s needs nor solely from the perspective of the children themselves. Instead, the desired solution is to combine the child’s experience, the perspectives of legal guardians and significant others and the healthcare professionals. Within this balance, however, it is important to always prioritise the children’s best interests in an attempt to optimise their well-being.^7^

To initiate a person-centred approach for paediatric care is to elucidate, listen to and affirm the child's narrative. Assessments of symptoms are essential in symptom relief for children with cancer, and self-reports are the gold standard for measuring symptoms.^8 9^

Children's own voices and self-reports are necessary to our understanding of the issues facing children if we are to reach the goal of symptom relief. 7 Children with cancer—like all children—have the right to actively take part in decisions regarding their health. In order to achieve this, they need support to communicate issues related to their symptoms. For such a system to work well in their everyday lives, symptom communication will largely rely on identification of symptoms, and communication skills and pathways to present this information in a timely and appropriate manner within their healthcare management.^10^

### Universal design

Healthcare professionals often tend to use language that is too complex for children to understand. Children can, therefore, be said to be ‘communication vulnerable’,^11^ depending on their level of health literacy, potential cognitive or communicative disabilities, age, language level or competency in the majority language.^12^ The Convention on the Rights of Persons with Disabilities put forth the idea of ‘universal design’ to the design of products, environments, programmes and services, so that they would be usable for all people, to the greatest extent possible, without the need for adaptation or specialised knowledge.^13^

The application of new digital technologies using pictorial supported communication may assist communication vulnerable children in healthcare to more effectively self-report and communicate with others about their symptoms, overcoming their and possibly their families’ communication difficulties. Pictorial communication support may foster closer relationships, trust and more open communication between families and healthcare professionals.^14^

### Self-assessment tools

The development of assessment tools for children to self-report pain started in the 1980s, with the widespread implementation of these tools in the 1990s.^15^ However, children’s self-reports have been shown to still fail to impact healthcare, and there is a need for innovative ideas that support the implementation of these assessment tools in clinical practice.^16 17^ Enabling children with cancer to self-report their symptoms may help them to understand their condition better and thereby better cope with their illness. Communicating symptoms in an effective way that can quickly alert healthcare professionals to their discomfort are empowering process that will make them feel secure in knowing that they have strategies that give them the possibility to communicate with somebody who will assist them to achieve symptom relief.^18^

Although validated patient self-report instruments exist for some symptoms, healthcare professionals seldom use these in clinical practice;^17^ furthermore, most paediatric conditions lack a validated symptom assessment tool. What is missing from the clinical toolbox is an instrument that assesses the intensity of symptoms in a simple, valid and reliable way.^19^ One of the few symptoms that is assessed in clinical practice is pain intensity. Smeland *et al* found that, overall, pain was assessed using a validated tool in 19% of the children in post anaesthesia care; this fell to 9% in children aged <5 years old.^17^ An explanation for this could be either that these instruments do not exist or that they are difficult to use, interpret or unreliable. Healthcare professionals prefer to rely on personal judgement and experience with the patient and family^20^ and, therefore, the measurement process must contribute to this and not try to replace it. The use of an instrument that focuses on a single symptom, for example, pain intensity, does not adequately capture the overall experience of the child and can be considered a restrictive application. Novel assessment tools that give a broader description of symptoms are, therefore, needed in order that the child can fully communicate their experience.

### Distress in children

The term ‘distress’ refers to a multifactorial unpleasant emotional experience that can be described as a combination of fear, anxiety and pain.^21^ The relationships between these factors are complex, and the experience of distress is based on interactions between ‘genetically linked behaviour patterns, temperamental predispositions, normal developmental fears, parental psychopathology and discrete learning experiences’.^22^ Distress in this study is defined as an experiential response and sensation of the mind associated with negative emotions that appear when a situation is fearful or impossible to manage from the perspective of the child. Distress can be a consequence of insufficient symptom relief, and self-reported distress is a global assessment that reflects the child’s experience of the success of symptom relief. It is important to evaluate the distress in children undergoing cancer treatment and to find strategies for the measurements of symptoms/emotions that are reliable and valid for this purpose. It is known that acute stress activates the hypothalamic–pituitary–adrenal axis and the sympathetic nervous system as well as the hypothalamic–pituitary–gonadal axis.^23–25^ For example, plasma cortisol concentration is an established stress (energy mobilisation) indicator that is known to react within minutes after the onset of stress exposure. Estradiol is on the other hand an anabolic hormone, which protects against adverse effects of stress.

### The medical scenario within which PicPecc will be tested

The drugs used to treat children with cancer can lead to several negative side effects, for example, children undergoing cancer treatment frequently report nausea and vomiting and other kinds of distress.^26^ One of the drugs that is used in cancer treatment is methotrexate, which is one of the most effective medications in the treatment of acute lymphoblastic leukaemia (ALL) in children.^27^ High-dose methotrexate is used world wide and has been included as part of the Nordic Society for Paediatric Haematology and Oncology ALL treatment protocols since 1981.^28^ Furthermore, the treatment is given according to a strictly detailed Nordic and European schedule, that is, clinical conditions have been well established. For these reasons, treatment with high-dose methotrexate has been chosen as the medical context within which the effect of the use of person-centred care for children (PicPecc) tool will be evaluated from a person-centred perspective.

The primary aim of the project is to investigate whether a person-centred communication intervention through the use of the PicPecc digital communication tool for children undergoing cancer treatment decreases the children’s symptom-related distress in general. A secondary aim is to investigate the process of implementing person-centred communication through the use of PicPecc tool.

### Main research question

Does adding the PicPecc tool decrease distress (measured on an 11-point numeric rating scale (NRS) (0 (no distress) and 10 (worst possible distress)) in children with ALL, aged 5–17 years, who undergo high-dose methotrexate treatment?

### Secondary research questions

Does the application of the PicPecc tool, increase person-centredness measured on Visual CARE Measure (VCM) in children with ALL, aged 5–17 years, who undergo high-dose methotrexate treatment?Does the application of the PicPecc tool alter stakeholders’ perspectives in a positive direction towards person-centred communication?

### Hypothesis

Children undergoing cancer treatment will experience lower distress levels, when they can report their holistic symptoms in a system created using universal design principles (ie, the PicPecc tool with pictorial support) than will children with standard healthcare communication opportunities (the primary outcome). In addition to a decrease in self-reported stress levels, there will also be a decrease in neuropeptides, neurosteroids and peripheral steroids for stress and pain.Person-centred care is enhanced, through enabling children to proactively assess their symptoms from a holistic perspective and communicate these to their healthcare providers within an enhanced communication framework (ie, using the PicPecc tool).

## Methods and analysis

### Study design

The Medical Research Council’s key principles and actions for development and evaluation of complex interventions^29 30^ guided the intervention development and the research design. In a hybrid design, both the effects of the intervention and the implementation process will be evaluated.^31^ Relevant care situations are selected^32^ where highly standardised care procedures are used and where there is a range of different situations where children struggle with symptoms. To facilitate the effect evaluation, the children will participate in a crossover design study where they are their own controls (figure 1). The study design follows the SPENT 2019 checklist for clinical trials.^33^

**Figure 1 F1:**
[figure not shown]
The cross-over design with two study groups will participate in two phases as related to the Nordic and European study protocols in Sweden for treatment of children with high-dose methotrexate. All methotrexate treatment sessions take a similar amount of time for the child. The intervals between each of the methotrexate treatments will be controlled by each child’s treatment plan and may vary between 3 and 6 weeks. NRS, numeric rating scale; PicPecc, pictorial support in person-centred care for children.

The development of the PicPecc tool follows established guidelines^34^ and was based on the theoretical framework of person-centred care,^4^ on published systematic reviews^9^ and on systematic reviews conducted within the project on assessment tools for nausea,^35^ and anxiety.^36^ Children with cancer, their legal guardians and healthcare professionals have been involved throughout the development process. The study protocol outlined here pertains to the evaluation and implementation phases.

### Participants and units

#### Context and setting

In Sweden, approximately 350 children are diagnosed with cancer each year. The treatment of childhood cancer is conducted at six childhood cancer centres and at regional hospitals.^37^ Three of these childhood cancer centres and five regional hospitals in Sweden will participate in the study.

### Selection criteria

Inclusion criteria are children diagnosed with ALL, between 5 and 17 years of age whose treatment plan includes at least two treatments of high-dose methotrexate. The child needs to have a cognitive level of at least 5 years (ie, to be able to understand an NRS).^38^ The child’s understanding of an NRS will be tested before inclusion based on a situational judgement test which involves a realistic, hypothetical scenario about a child who fell from a tree. The child will be asked to assess pain using the NRS. This situational judgement test has previously been validated to discriminate positive and negative emotions.^39^ Exclusion criteria are children 0–4 years, no verbal assent from children unable to read, scheduled to undergo only one high-dose methotrexate treatment.

The inclusion criteria for legal guardians will be that their child has undergone the high-dose methotrexate treatment and has used the PicPecc tool. In addition, legal guardians will need to be at the hospital during the treatment.

The inclusion criteria for healthcare providers will be that they are responsible for the children’s care during the high-dose methotrexate treatment when the children use the PicPecc tool.

### Method of recruitment

The recruitment is planned to start at the beginning of 2021. The surveyed children participate in data collection two times, once as a control (A) and once at the time of symptom reporting and initial use of the communication tool PicPecc (B) (figure 1). Children with cancer aged 5–17 years old, legal guardians and healthcare professionals at three childhood cancer centres and five regional hospitals in Southern Sweden will participate in the study. Each year approximately 175–200 children get cancer in Southern Sweden, and about a third of these children receive a diagnosis of ALL. At the three childhood cancer centres and at the five regional hospitals included in this study, approximately 25 of these children will fulfil the inclusion criteria for this study each year.

Healthcare providers at each of the units will be interviewed. The nurse and/or nurses who initiate and conclude the high-dose methotrexate treatment will be invited to a semistructured interview.

### Consent process

Legal guardians of children below 15 years of age with ALL who are scheduled to receive high-dose methotrexate treatments will be informed about the study by a physician or a nurse, included in the research group. The legal guardian will receive written information, and the child will be given text and picture-based information. On consent from a legal guardian, child assent is obtained verbally and in writing if the child can read. Older children (aged 15 years or above) will give written consent themselves. In Sweden, children between 15 and 18 years can provide written informed consent themselves if they are assessed to have the level of maturity and capacity to understand the consequences of participation.

### Randomisation

The participants will be allocated codes in a consecutive order; the code is randomly assigned to either the intervention phase (B) or control phase (A). Participating cancer units will be given the solution to the randomisation code once the codes have been allocated to the participants. The participants will only have access to the PicPecc tool during the intervention phase. There will be a period of at least 2 weeks between the end of the first intervention period and the start of the next methotrexate treatment. This provides an adequate washout period between the intervention (B) and the control phase (A) for any behaviour change to revert to previous patterns. Following the transtheoretical model,^40^ habitual behaviour change related to health is a process involving a number of stages that takes time to complete successfully, where support for change is removed early in the process the individual will quickly revert to previous habituated behavioural patterns. We are confident, therefore, that the intervention will have no residual effects on the control phase.

### Measures and materials

#### Impact evaluation

We consider a difference of 15% to be a meaningful difference in score average between T0 and T2 (48 hours); this is represented by a difference of approximately 1.5 units on the NRS (0–10) of distress, when comparing users of the PicPecc tool to control subjects. The estimate of SD is based on unpublished data of 11 to 12-year-old girls’ self-reports.^41^ Based on an expected SD of 2.9 (and a power of 0.8), it is necessary to include at least 32 participants. With a dropout rate of approximately 20%, 20 participants in each group, that is, 40 participants will be included in the study.

In both the control (A) and intervention phases (B), the data collection follows the test period outline in figure 2. Assessment of distress will be made at time points T-1, T0, T1 and T2. T3 is an interview to evaluate the implementation process. Primary outcome is the difference in delta T0 and T2 between control and intervention phases. The time points are linked to the schedule for the methotrexate treatment to avoid extra blood sampling. The time points will also facilitate the evaluation between before and after treatment, with the objective to evaluate differences in symptoms, with and without the PicPecc tool (figure 2).

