**Figure 2 F2:**
[figure not shown]
Data collection time points and variables in both the control and intervention phases. BMI, body mass index; NRS, numeric rating scale; PicPecc, pictorial support in person-centred care for children.

Primary outcome:

The change in the primary outcome variable (distress) from baseline (T0) to 48 hours after treatment start (T2) measured on an 11-point NRS (0 (no distress) and 10 (worst possible distress))^42 43^ will be compared between the control and intervention phases. Self-reported distress (NRS-11) will also be collected 4 hours before high-dose methotrexate (T-1) and after 24 hours (T1) (figure 2) in order to establish within subject variation.

Secondary outcomes:

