### Data analyses plan

#### Effect evaluation

We expect the intervention to be superior to the control in terms of the health outcome assessment (NRS-11). We also expect that there will be a difference between premethotrexate treatment (T1, T0) and methotrexate treatment (T1, T2) in both intervention and control phases. Therefore, we will test the null hypothesis that there will be neither change in any of the measurements between the premethotrexate treatment (T-1, T0) and methotrexate treatment (T1, T2) nor between intervention and control phases. A p value of <0.05 will be considered as statistically significant. Categorical data will be descriptively analysed by frequency distributions and percentages. The paired sample t-test will evaluate the difference between two sets of assessments and effect size.^47^ Data will be analysed with IBM SPSS Statistics V.25 (New York City, USA).

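### The primary analysis compares raw T0–T2 changes between phases. Adjusting T2 for the T0 difference would usually be more precise, provided the baseline precedes use of the tool.

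*Protocol article*

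**What the plan says.** Under Impact evaluation, the protocol article defines the endpoint: "Primary outcome is the difference in delta T0 and T2 between control and intervention phases". The primary outcome paragraph after the Figure 2 caption repeats it: "The change in the primary outcome variable (distress) from baseline (T0) to 48 hours after treatment start (T2", at 48 hours, is compared between the control and intervention phases.

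The Effect evaluation section of the data analyses plan names the test: "The paired sample t-test will evaluate the difference between two sets of assessments and effect size". No baseline covariate is mentioned. The threshold is given as "A p value of <0.05 will be considered as statistically significant", without saying whether it is one- or two-sided.

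The sample size rests on a meaningful difference ("this is represented by a difference of approximately 1.5 units on the NRS") and then: "Based on an expected SD of 2.9 (and a power of 0.8), it is necessary to include at least 32 participants". The source of the SD is described only as follows: "The estimate of SD is based on unpublished data of 11 to 12-year-old girls’ self-reports". Enrolment is set by "With a dropout rate of approximately 20%, 20 participants in each group, that is, 40 participants will be included in the study".

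Two other statements matter here. Distress is scored at T-1, T0, T1 and T2 in both phases, so a baseline exists for every child in each phase. The Intervention section has the child using PicPecc before methotrexate as well as during it. The text does not say whether T0 in the intervention phase comes before first use of the tool (Figure 2 is not shown).

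**The concern.** In a crossover, anything stable about a child cancels when the control phase is subtracted from the intervention phase. The usual reason for a change score, removing stable between-child differences, has therefore already been met by the design. Subtracting T0 within each phase brings in two further readings of a single 0–10 item, with the weight fixed at 1 whatever the data show. If T0 predicts T2 only moderately within a child, that weight is too large and the noise added exceeds the noise removed.

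What is at stake is precision in a trial planned on 32 evaluable children. The SD comes from unpublished data in one narrow age and sex group, so any margin in power is useful.

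**Working it through.** **1. The plan's own figure.** Inputs from Impact evaluation and Effect evaluation: difference 1.5, SD 2.9, power 0.80, alpha 0.05. The article does not say what 2.9 is the SD of. Read it as the SD of the within-child difference in changes, and take a two-sided paired t-test with the noncentral t distribution:

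- n = 32, power 0.809. The normal approximation gives 30 and a one-sided t-test gives 25, so the two-sided t-test is the reading that matches.
- Dropout: 32 / (1 − 0.20) = 40, as stated.
- Planned standard error: 2.9 / √32 = 0.513.

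**2. Variance of the two analyses.** For each child let D2 = T2(B) − T2(A) and D0 = T0(B) − T0(A), where A is the control phase and B the intervention phase. Assume both have variance σ², and let β be the slope of D2 on D0.

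- Change score: Var(D2 − D0) = 2σ²(1 − β)
- Adjusted for D0: Var(D2 | D0) = σ²(1 − β²)
- Ratio, change score over adjusted: 2 / (1 + β)

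The change score is also less precise than T2 alone when 2(1 − β) > 1, that is, when β < 0.5.

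**3. Assumed slopes.** The article gives no correlation. Assume a cross-phase correlation of 0.3 and a within-phase T0–T2 correlation of 0.5, 0.6 or 0.7. Then β = (0.5 − 0.3)/(1 − 0.3) = 0.29, and likewise 0.43 and 0.57.

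**4. Power.** The adjusted variance is 2.9² × (1 + β)/2, inflated by 1 + 1/(n − 3) for estimating the slope (1 + 1/29, about 3%, at n = 32), with n − 2 degrees of freedom.

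| β | Variance ratio 2/(1+β) | SE at n = 32 | Power at n = 32 | n for 80% power |
|---|---|---|---|---|
| plan (change score) | – | 0.513 | 0.81 | 32 |
| 0.29 | 1.55 | 0.42 | 0.93 | 23 |
| 0.43 | 1.40 | 0.44 | 0.91 | 25 |
| 0.57 | 1.27 | 0.46 | 0.88 | 27 |
| 0.90 | 1.05 | 0.51 | 0.81 | 31 |
| 1.00 | 1.00 | 0.52 | 0.795 | 33 |

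If sequence is fitted too, the degrees of freedom fall from 31 to 29. The inflation is then at most about 1 + 2/28, or 7%, and the first three sample sizes become 24, 26 and 28.

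**5. Unequal variances.** In general the slope is r × SD(D2)/SD(D0). If SD(D0) is 0.7 of SD(D2) and r = 0.7, the slope is 0.7/0.7 = 1. In units of Var(D2), the change-score variance is 1 + 0.49 − 2 × 0.7 × 0.7 = 0.51 and the adjusted variance is 1 − 0.49 = 0.51. There is no gain. Power is 0.795 against 0.809, or about 0.78 with sequence fitted.

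**6. If the tool has already moved T0.** Suppose the tool lowers T0 by 1 and T2 by 1.5. The change score estimates −1.5 − (−1) = −0.5. The adjusted contrast estimates −1.5 + β, which is −1.2, −1.0 and −0.8 for β = 0.3, 0.5 and 0.7. A simulation of 20,000 trials of 32 children gave the same values. Neither analysis recovers −1.5.

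**The case against.** The planned test is an accepted and valid one, and it agrees with the stated sample size. Nothing shows bias in it or an error in the 32 or the 40. A reader might infer from the variance formula that the trial is wrongly sized or its primary test invalid. The documents support neither inference: under the reading of 2.9 used here, the planned test delivers its stated power.

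A reader might also infer that adjustment estimates the same effect at no cost. That goes too far. The two analyses target the same effect only if the tool has not touched T0, and the Intervention section leaves that open. Randomised phase order does not repair a covariate measured after exposure. The cost is small but not nil.

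Nor is it right that only a near-perfect T0–T2 correlation removes the gain. That holds under equal variances. Distress before treatment and at 48 hours, on a bounded scale, may well differ in spread, and step 5 shows the gain gone at r = 0.7.

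Finally, covariates are often left to an analysis plan, and none is shown. That would answer a complaint about missing detail. Here the article states both the endpoint and the test, so the point concerns a stated choice.

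These objections limit the size of the claim and attach a condition to it. They do not make the change score preferable. When the slope is near 1 the loss from adjusting is 1–3 points of power, against a gain of about 7–12 points over the assumed slopes.

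**Conclusion.** The point holds as one of efficiency. The stated primary analysis is valid but usually less precise than T2 adjusted for the within-child T0 difference. For slopes of 0.29–0.57 its variance is about 1.3 to 1.6 times the adjusted variance, before the small cost of estimating the slope.

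The result rests on four assumptions: the slopes, which the article does not give; equal variances at T0 and T2; 2.9 being the SD of the paired difference in changes; and a T0 unaffected by the tool. The third affects the power figures but not the variance ratio. The fourth matters most, because a baseline already shifted by PicPecc distorts both analyses, and in the example of step 6 it distorts the change score more.

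**What to change.** Before outcome data are examined:

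- Define the primary comparison as T2 distress, intervention versus control phase, adjusted for the child's between-phase difference in T0, with period in the model. In practice, regress D2 on D0 and a centred sequence indicator, and report the adjusted mean difference at D0 = 0.
- Keep the T0–T2 change, compared between phases, as a supportive analysis.
- State that the baseline reading used precedes first access to PicPecc in the intervention phase. If T0 follows first use, use T-1 in both phases, provided T-1 precedes it. T-1 would have its own slope, so the figures above would not carry over exactly.
- State what the SD of 2.9 refers to.

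The cost is one degree of freedom for the baseline and a second for sequence, about 3–7% variance inflation at 32 children, and a revision of the analysis text. No new assessments are needed, provided T0 or T-1 already precedes first tool use. If neither does, data collection would have to change as well.
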